## Abstract

**Background:**

Anticipatory guidance around the management of sleep and crying problems in early infancy has been shown to improve both infant behaviour and parent symptoms of postnatal depression. Digital technology offers platforms for making such programs widely available in a cost-efficient manner. However, it remains unclear who accesses online parenting advice and in particular, whether the parents who would most benefit are represented amongst users. It is also unknown whether the uptake of online programs can be improved by health professional recommendations, or whether parents require additional prompts and reminders to use the program. In this study we aim to: (1) determine whether weekly email prompts increase engagement with and use of a brief online program about infant sleeping and crying, (2) determine whether encouragement from a maternal and child health nurse promotes greater engagement with and use of the program, (3) examine who uses a brief online program about infant sleeping and crying; and, (4) examine the psychosocial characteristics of participants.

**Methods/Design:**

This study is a randomised, parallel group, superiority trial, with all participating primary carers of infants aged 2 to 12 weeks, receiving access to the online program. Two modes of recruitment will be compared: recruitment via an online notice published on a non-commercial, highly credible and evidence-based website for parents and carers and via the parent’s Maternal and Child Health nurse. After baseline assessment, parents will be randomised to one of two support conditions: online program alone or online program plus weekly email prompts. Follow up data will be collected at 4 months of infant age.

**Discussion:**

Results from this trial will indicate whether involvement from a health professional, and/or ongoing email contact is necessary to engage parents in a brief online intervention, and promote parental use of strategies suggested within the program. Results of this trial will inform the development of recruitment and engagement strategies for other online interventions.

**Trial registration:**

Australian New Zealand Clinical Trials Registry: ACTRN12613001098729. Registered 01 October 2013.

## Background

Infant sleep and crying are common concerns for parents of infants [1] with 12 to 27 % of parents reporting infant crying problems within the first 4 months [2, 3], and 16 to 38 % of parents reporting infant sleep problems within the first year [2–4]. Common parent concerns centre on the amount and pattern of their infant’s sleep, strategies for settling, and how to best manage infant crying [5]. Evidence suggests that anticipatory guidance delivered face-to-face, helps parents to establish good infant sleep habits, reduces parent distress about normal infant crying, and reduces postnatal depression (PND) symptoms [3, 6–10]. However, it has not been determined whether this type of approach can be effectively delivered online. The internet potentially offers a cost effective and convenient platform for delivery of anticipatory guidance to large and geographically diverse audiences. Currently, little is known about the characteristics of parents who particpate in online programs during the early postpartum period, or how to best enhance recruitment and maintain engagement with the program content. An evidence based program, *Cry Baby*, was developed for online delivery. The aim of this study is to examine the characteristics of parents (and their infants) who seek help for infant behaviour via a parenting website, and identify any under- or over- representation of population subgroups within the sample. We also seek to determine whether encouragement from a health professional to take part in an online program, and/or regular weekly email support, promotes greater engagement with the program and greater use of suggested strategies.

Infant sleep problems are common (38 % of parents of 4 week old infants report infant sleep problems) [3], costly to treat [11], and are associated with increased risk of PND [12] and parental fatigue [13]. A number of randomised controlled trials have shown that behavioural-education interventions that give advice on how to set up good sleep habits in infancy can successfully prevent problems with infant settling and night waking [3, 6–10]. These interventions promote parenting efficacy; enhancing parent confidence and competence with managing infant sleep and crying behaviours [10].

Infant crying is normal and has a natural peak in frequency of around 2.5 h of crying per day at around 6–8 weeks of age [1]. While infant crying rarely has a medical cause [14], 27 % of parents report their infant’s crying is a problem and many of these parents will seek assistance in the belief that something is medically wrong [2, 3]. Educating parents on normal infant crying behaviour may reduce parental distress and the incidence of parents unnecessarily seeking costly medical support. Additionally, providing parents with advice on strategies for coping with infant crying, may help prevent cases of Abusive Head Trauma (AHT; previously known as Shaken Baby Syndrome) [15]. Frequent infant crying is a proximal risk factor for AHT, and is potentially more readily modifiable than other risk factors such as being of low socioeconomic status, or born prematurely [16].

Mothers who report infant sleep and crying difficulties are at increased risk for PND [12, 13, 17–19]. In a short-term longitudinal study, Goldberg and colleagues [18] found that mothers who were experiencing symptoms of distress at 6 months had infants with more sleep and crying issues, and reported being more bothered by those issues. This trend was still apparent when the infant was 12 months of age. Hiscock and colleagues [20] found that providing parents with a brief behavioural intervention delivered by a primary healthcare professional at 8 months of infant age was effective in reducing infant sleep problems and improving maternal mental health. Early intervention for unsettled infant behaviour, may reduce the risk of ongoing maternal symptoms of depression and distress through later infancy. Emerging research also suggests that infant sleep and settling problems may impact on parental fatigue [13]. In an Australian sample Giallo and colleagues [13] found the mothers of young children (0–4 years) with sleep and settling difficulties had an increased risk of experiencing high levels of fatigue, with the potential for adverse impacts upon their daily functioning, parenting and later child outcomes.

Several research trials have established the effectiveness of interventions designed to improve infant sleep or help parents manage infant crying [7, 9, 10, 21, 22]. An Australian randomised controlled trial evaluated the *Baby Business* program, which provided anticipatory guidance on infant sleep and crying with content delivered via booklet, DVD, telephone consultation and a parent group session [3]. Compared to the control condition, the program resulted in significantly better outcomes for mothers and infants, including a greater decline in PND symptoms from 4 to 6 months post-natally, less time spent attending to the infant during the night, fewer changes to infant formula to ‘manage’ infant behaviour, less doubt about settling the infant at bedtime and better ability to set limits at bedtime. Additionally, mothers of a sub-group of infants that were ‘frequent feeders’ (fed greater than 11 times per 24 h) reported fewer daytime sleep and crying problems. These findings bode well for the prevention of future sleep problems in these infants.

While the efficacy of face-to-face interventions has been established, low income parents and those residing outside of major metropolitan areas, face major obstacles to accessing parenting interventions. Key barriers include difficulties with transportation, problems accessing childcare to attend appointments, and inflexible work hours [23]. Studies have shown that mothers of young children frequently consult the internet for information about their children’s health [24–26] and social isolation amongst young mothers is associated with greater amounts of time spent online overall [27]. A study from the Royal Childrens Hospital (Melbourne, Australia) indicated that 81 % of mothers had access to the internet and 18 % had changed the way they managed their children’s health based on information found online [28]. While the internet offers the potential for better access to evidence-based interventions for vulnerable, low income and/or remote families, particularly via the ubiquitous smartphone, little is known about actual uptake of online interventions by these families. Given the higher adoption rates of home internet connection and smartphone ownership in higher income groups [29], it is possible that online programs that target infant sleep and cry problems will attract the same over-representation of parents who are more highly educated and of higher socioeconomic status, as traditional face-to-face interventions [3].

One way this imbalance may be addressed is for infant health care providers to encourage participation. In the Australian state of Victoria all newborn infants are assigned a Maternal and Child Health (MCH) nurse, who provides free health checks at 7 to 10 days, 2 weeks, and then at 1, 2, 4, 8, 12, 18, 24 and 42 months of age. Access is almost universal – 98 % of infants participate in the first (in-home) visit, and 96.6 % attend the MCH clinic for the 2 week (infant age) check up [30]. MCH nurses are in a unique position to direct parents to suitable evidence-based online interventions that are specific to the first few weeks postpartum, because they have frequent contact with parents during this time. In addition, evidence suggests that support or encouragement from nurses or other health professionals during online program participation helps to keep parents engaged [31, 32]. A strategy often employed to increase engagement and retention to online programs, is the use of email prompts, however, little research has specifically examined their effectiveness. Email prompts have been shown to increase the number of adults who returned to computer tailored lifestyle interventions (targeting smoking behaviour and fruit and vegetable intake, for example) [33], and this effect was increased when the prompt occurred soon (2 weeks) after initial program login [34], but we can find no research that evaluates the usefulness of email prompts in samples of parents of infants, whose needs and time demands would be quite different. Uptake of, and retention to, online programs varies considerably, but is generally reported to be lower than anticipated (~2–10 % and ~15–97 %, respectively) [35–39]. If online interventions are intended to be used broadly, then evidence for strategies employed to engage and retain participants, will be necessary.

Research examining the reach and acceptability of online parenting programs is still in its infancy, however, results so far look promising. A trial of an online intervention designed to treat *existing* sleep problems in infants/toddlers aged 6 to 36 months, resulted in increased infant and mother sleep duration, and reduced infant sleep onset latency [39]. Participant retention to the trial at follow up was very high (97 %) however a financial incentive was offered to parents who took part (ranging from $90–$175), making it difficult to determine how many parents would engage with online programs without an incentive. Other trials have demonstrated the effectiveness of online programs for a variety of purposes including educating parents on child mental health [40], increasing positive body image in adolescents [41] and treating child anxiety [42], to name a few. Online programs targeting mental health have also been useful for those in a rural or remote setting [43].

While the effectiveness of face-to-face interventions for *preventing* infant sleep and crying problems has been consistently supported, to the authors’ knowledge, there have been no trials examining whether the same advice can be effectively delivered via an online program. Such an approach may be particularly appropriate for parents who face complex and competing demands in the first few weeks postpartum. Parents may favour a resource that can be accessed at any time day or night; can be quickly and easily navigated; and that allows access to specific relevant content when the parent needs it. Initial encouragement from a MCH nurse, and/or onging participant support via email, may also be helpful in bolstering parent engagement and rentention to the program. Such strategies would be relatively easily built in to existing postpartum health services or as a feature in an online platform. With this in mind, the *Cry Baby* online program was developed. The current research aims to examine factors influencing participant engagement and retention to the Cry Baby online program, with the intention that results will inform the design of a larger efficacy trial.

### Study objectives

Our objectives are to examine:whether randomisation of participants to a condition that receives additional email prompts that encourage parents to log in to the program, will result in greater use of program strategies (primary outcome) as well as greater retention to the research at follow-up (at 4 months of infant age)whether parents who have the program recommended by their MCH nurse are more likely to engage with the program (as measured by program completion rates), than those who are recruited via an online advertisement for the program; and, whether they are also more likely to use the suggested strategiesthe demographic profile of parents who choose to take part in the online program with a view to identify any over- or under-representation of parents (compared to Australian Census data where possible) based on: household income, socioeconomic status, education, language spoken and support available to parents; or child characteristics, including birth order of infant, infant age, gender, birth weight, gestation, and where the baby sleeps at night; and, to see how this differs for participants who are recruited via a popular parenting website compared to those recruited via their MCH nursethe psychosocial well being of participants (specifically depression symptoms, fatigue and cognitions surrounding infant sleep in parents, and in infants, night waking behaviour, and, sleep, crying or feeding problems), with a view to identify any specific concerns that may be addressed in the development of new online programs for parents of infants

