Recruiting some of our sample from Australian wide online advertising and some from a specific region, introduces systematic differences to the groups. In an attempt to reduce this as much as possible, we selected the Melbourne (state of Victoria, Australia) Local Government Area (LGA) of the City of Yarra for MCH nurse recruitment, due to both its high birth rate per annum [45], and broad cultural and socioeconomic diversity [46]. All MCH nurses within this LGA (11) will invite parents of infants attending the 2 week appointment to participate in the trial. The 2 week appointment will be specifically targeted as it was suggested by the nurses that this appointment is less intensive than the in-home appointment at 7–10 days postpartum, and it is unusual for parents of infants aged less than 2 weeks to request information on infant sleep and crying so soon after birth. Recruitment will run for a 12 week period and will allow for later determination of the percentage of parents in the general community that are likely to take part in an online program if suggested by their MCH nurse (birth rate data for this region, throughout this time period will be compared to our sample). MCH nurses will provide parents with a postcard, inviting them to participate in the program. The postcard will contain brief information about the study and a link to the study website so they can gain further information about the research. Participants who indicate that they heard about the Cry Baby program via their nurse *and* via online advertising will be classified as having been recruited via their nurse since it is the effect of encouragement from a health professional that we aim to examine. The Cry Baby program is currently only available to those willing to take part in the research trial and has not been broadly advertised outside the Raising Children Network. This means it is very unlikely that parents would have the program suggested to them by other health professionals.

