#### Baseline questionnaire

The participant will be asked to complete a baseline questionnaire online. This will collect demographic information about the parent (age, gender, educational attainment, employment status, country of birth, main language spoken at home, and household income) and infant (birth order, date of birth, gender, birth weight, gestation, and where the baby sleeps at night). Area-level socioeconomic disadvantage will be determined using the *Socio-economic Indexes for Areas* [46] based on participant postal code and population census data.

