##### Online program usage

Data will be collected via the programming of the online system, recording whether the program was completed (if all program modules were accessed for a minimum of 1 min each), how many times the participant logged in to the program, and how much time in total they spent within the program.

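### The nurse-versus-website contrast covers enrolled parents only and uptake has no website-only comparator, so it cannot show whether nurse involvement raises uptake or is needed to engage parents

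*Protocol article*

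**What the plan says.** The Abstract (Background) sets out the gap: "It is also unknown whether the uptake of online programs can be improved by health professional recommendations". The aim that follows is worded differently, to "determine whether encouragement from a maternal and child health nurse promotes greater engagement with and use of the program". The Study objectives section fixes the measure for that aim: whether nurse-referred parents "are more likely to engage with the program (as measured by program completion rates), than those who are recruited via an online advertisement", and whether they also use the strategies more. Outcome measures adds that the primary outcome, frequency of strategy use, will be compared by recruitment mode as well as by trial arm.

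Completion is logged by the online system, "recording whether the program was completed (if all program modules were accessed for a minimum of 1 min each" being the definition (Online program usage). Strategy use comes from the follow-up questionnaire. Access is confined to participants: "The Cry Baby program is currently only available to those willing to take part in the research trial" (Study setting and recruitment).

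The same section plans one uptake figure, the "percentage of parents in the general community that are likely to take part in an online program if suggested by their MCH nurse", for which "birth rate data for this region, throughout this time period will be compared to our sample". For the website stream the protocol gives only an annual count of site visits, 5.7 million. The Abstract (Discussion) and the main Discussion say that the results will show whether a health professional has to be involved for parents to engage.

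**The concern.** A nurse's recommendation acts first on whether a parent signs up. A comparison of completion among those who signed up conditions on that step. The protocol's own rationale makes this relevant. The Background expects online programs to over-represent educated, better-off parents and offers encouragement by health care providers as one way to correct this. If that works, the nurse stream will contain parents whom the website alone would not have reached. Should they finish the program less often, the nurse route can look weaker on completion because it recruited successfully.

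The single uptake figure does not repair this. It has no counterpart without a nurse. Parents who heard of the program from both sources are counted as nurse-recruited, so the figure also includes some who might have joined from the website anyway.

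At stake is the reading of the second aim. The results are meant to guide recruitment to other online programs and a larger efficacy trial. A statement that nurse involvement is, or is not, needed would rest on a contrast that does not measure it.

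**Working it through.** **No planned figure to reproduce for this contrast.** The protocol's only sample size concerns the email comparison. With a difference of 0.5 SD, two-sided 5% and 80% power, n = 2 × (1.960 + 0.842)² / 0.5² = 62.8, so 63 per arm and 126 in total, as stated. It does not bear on recruitment mode, which is not randomised.

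**Who each quantity is observed for**

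| Quantity | Nurse stream | Website stream |
|---|---|---|
| Uptake | Enrolments against births in the region | No denominator |
| Completion | Enrolled parents | Enrolled parents |
| Strategy use | Enrolled parents | Enrolled parents |

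The only row that could answer the uptake question has one filled cell.

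**Can the ranking differ between the two scales?** Let u be uptake and c completion among enrolees. Completers per 100 parents = 100 × u × c. The protocol gives neither u nor c for either stream, so every value below is assumed. Uptake is kept within the roughly 2–10% that the Background quotes for online programs in general.

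- Nurse: u = 8%, c = 40%, giving 100 × 0.08 × 0.40 = 3.2.
- Website: u = 2%, c = 60%, giving 100 × 0.02 × 0.60 = 1.2.
- Ratio: 3.2 / 1.2 = 2.7 in favour of the nurse route, while the planned contrast reads 40% v 60% against it.

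**When does it reverse?** With these completion rates, the nurse route yields more completers when 0.40 × u(nurse) > 0.60 × u(website), that is, when u(nurse) / u(website) > 1.5. With 2% uptake in both streams the result is 0.8 v 1.2, ratio 0.67, and the nurse route is lower on both scales.

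**The mechanism made explicit.** Suppose website joiners would join by either route and complete at 60%, and the nurse adds further parents. Completion among nurse enrolees = [u(website) × 60% + (u(nurse) − u(website)) × c(added)] / u(nurse).

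| Website uptake | Nurse uptake | Completion in added parents | Completion among enrolees, website v nurse | Completers per 100, website v nurse |
|---|---|---|---|---|
| 2% | 10% | 40% | 60% v 44% | 1.2 v 4.4 |
| 5% | 10% | 40% | 60% v 50% | 3.0 v 5.0 |
| 5% | 10% | 20% | 60% v 40% | 3.0 v 4.0 |
| 2% | 10% | 60% | 60% v 60% | 1.2 v 6.0 |

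The nurse route has more completers in every row by construction, because the model assumes that nurses add parents and lose none. The table shows that the two scales can disagree, not that they will. If added parents complete as often as the others, completion is tied and no reversal occurs.

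**The case against.** The strongest reply is that uptake is not a stated objective. The sentence on uptake is background, the second aim speaks of engagement and use, the objective defines engagement as completion, and no uptake outcome is listed. Engagement among participants is a legitimate question, and the planned contrast addresses it. The nurse-region percentage is a descriptive by-product offered without a claim of contrast. This stands, and it limits the point: the fault is a mismatch between the question posed and the conclusion promised on one side and the measure fixed on the other. It does not remove the conclusion printed in the Abstract and Discussion.

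The protocol also admits systematic differences between the recruitment groups, and its third objective compares who enrols by each route. That helps to describe the selection. But the admission concerns the region from which families come, and a profile of enrolees does not say how many parents were reached or would have joined without a nurse.

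Three stronger readings are not supported:

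- A reader might infer that the trial will get the nurse effect backwards. That needs added parents who complete less often and a sufficient gain in uptake, and the protocol has data on neither.
- A reader might infer that the distortion would persist with identical families in both streams. It would persist with identical source populations. If the enrolled families were identical, it would vanish.
- A reader might take website uptake as 1% and obtain 3.2 v 0.6, a ratio of 5.3. That value lies below the range the protocol quotes.

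**Conclusion.** The point holds as a mismatch between conclusion and contrast. It is fact, read from the protocol, that both nurse-versus-website outcomes are confined to enrolled parents and that uptake is estimated in one stream only, without a website-only comparator. It follows that the planned contrast cannot support a statement about uptake, or about whether nurse involvement is needed for parents to engage.

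That the contrast could also rank the routes in the opposite order from total completers is a possibility. In the assumed example the completers differ by a factor of 2.7 in the direction opposite to completion. This rests on invented uptake and completion rates, and at those completion rates it needs nurse uptake above 1.5 times website uptake. The contrast remains usable for the narrower question of how far parents who enrolled by each route went on to complete the program, subject to the regional differences that the protocol already acknowledges.

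**What to change.** In the second objective, and in the matching statements in the Abstract (Discussion) and the Discussion, say that the nurse-versus-website contrast applies among enrolled parents. Base no statement about uptake, or about whether a health professional's involvement is needed, on it. Report uptake in the nurse region as a descriptive figure without a comparator. This is a change of wording and costs almost nothing.

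Optionally, add an exploratory table of enrolments and program completers per 100 births in the City of Yarra and in councils named in advance where the website notice is the only route, with rate ratios and confidence intervals. Postcode is already collected: area-level disadvantage is to be derived "based on participant postal code and population census data". Calendar periods and infant-age windows must be matched, since the Procedures section gives 12 weeks per modality without saying that they coincide, and nurses invite at the 2 week visit while website parents may have infants aged up to 12 weeks.

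The cost is birth data for further councils, which the plan does not now gather. With a recruitment target of 152 and a website stream drawn from all of Australia, website enrolees in any few councils may be very few. The comparison would also be non-randomised, so the table could only be descriptive.

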#### Follow-up questionnaire

A secure web link to the follow-up questionnaire will be emailed to participants when their infant is 16 weeks of age. This represents an age at which most infants ‘sleep through the night’ (i.e., achieve 5 consecutive hours of uninterrupted sleep during the night) [49].

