##### Caregiver support

Participants will rate the level of support or help they received from (1) their partner, (2) family and friends living elsewhere (i.e., I get enough help, I don’t get enough help, I don’t get any help, I don’t need any help), and (3) how often they feel they need support or help but can’t get it from anyone (i.e., very often, often, sometimes, never, I don’t need it) [50]. These items have previously been used in the Longitudinal Study of Australian Children [50] and in the *Baby Business* trial [3].

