### Procedures

The recruitment phase will run for 12 weeks in each recruitment modality. An advertisement placed on the Raising Children Network will provide interested parents with a link to the program’s online landing page. MCH nurses will provide all parents of newborn infants at the 2 week infant check with an advertising postcard containing the link to the landing page.

The landing page will provide more information describing the study, what participation involves, and a secure link to the online baseline survey where participants can read the projects’ plain language statement and complete eligibility criteria and consent. After completion of the baseline survey, participants will receive email notification of their allocation to condition (i.e., *Cry Baby* alone or *Cry Baby with Additional Prompts*). The final page of the baseline survey will provide participants with a secure link to the *Cry Baby* website, where they can register their login details and immediately access the *Cry Baby* program.

All participants will receive a welcome email which contains further information about the program and their group allocation. Participants allocated to the *Cry Baby with Additional Prompts* condition will also receive a brief, age-appropriate email prompt each week (from 2 weeks of infant age) until their infant reaches 12 weeks of age. Each email will contain a brief summary of information from the online program.

When participants’ infants are approximately 16 weeks of age, they will receive an email link to the follow up survey which has their unique ID code embedded. If participants have not completed their follow-up questionnaire after 2 weeks, a reminder email will be sent a maximum of three times over a 6 week period. At this time point, some parents will only have had access to the program for 4 weeks, and others for 14 weeks, however, we expect that if parents are going to try out strategies suggested in the program, they would do so within 4 weeks of their first access to the program. Setting the follow up time point according to infant age, rather than time since enrolment, controls for the large variability in infant development that might otherwise impact on our results.

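### Objective 3 profiles enrolling parents on available support, but the support items are listed only in the 16-week follow-up questionnaire, so this one variable describes follow-up respondents

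*Protocol article*

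**What the plan says.** **Study objectives (third objective).** The target is the group of parents who enrol. The aim is to see which groups are over- or under-represented, against Census data where that is possible, and how website recruits differ from nurse recruits. The parent characteristics named are "household income, socioeconomic status, education, language spoken and support available to parents". A list of child characteristics follows.

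**Baseline questionnaire.** The section itemises what is asked. The parent items are "age, gender, educational attainment, employment status, country of birth, main language spoken at home, and household income" and the infant items are "birth order, date of birth, gender, birth weight, gestation, and where the baby sleeps at night". Area-level disadvantage is derived from the postcode. No support item appears.

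**Follow-up questionnaire.** "A secure web link to the follow-up questionnaire will be emailed to participants when their infant is 16 weeks of age". The Caregiver support subsection stands under this heading: "Participants will rate the level of support or help they received from (1) their partner, (2) family and friends living elsewhere". A third item asks how often help is needed but cannot be had from anyone.

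**Procedures.** When the follow-up link goes out, "some parents will only have had access to the program for 4 weeks, and others for 14 weeks". Non-responders are then reminded over a further period of weeks, so some answers come later still.

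**Statistical methods.** All analyses control for child age, and Full Information Maximum Likelihood is planned for missing follow-up data.

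**The concern.** A profile of who enrols needs characteristics measured at enrolment, on everyone who enrols. Support fails on both counts.

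- *Who is measured.* Only parents who return the follow-up survey supply an answer. The first objective itself expects the email prompts to raise retention, so the respondents may be a selected group, and selected differently by arm.
- *When it is measured.* The rating is given at an infant age of 16 weeks or more, after a period of program access that varies from parent to parent. Nurse recruits are invited at the 2-week check, whereas website recruits may join at any age up to 12 weeks. The length of access before the rating can therefore differ by recruitment mode, which is the contrast the objective wants to make.

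At stake is one line of the participant profile and one line of the website-versus-nurse comparison. Both would be read as statements about enrolling parents when they are statements about later respondents. An enrolment rating that was never taken cannot be recovered afterwards.

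**Working it through.** **1. Match each characteristic in the objective to its place of collection.**

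- Household income, education, language: baseline.
- Socioeconomic status: baseline, through the postcode.
- Birth order, infant age (from date of birth), gender, birth weight, gestation, sleeping place: baseline.
- Support: Caregiver support, under the follow-up questionnaire. It is not in the baseline list, and no other section places it at enrolment.

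Support is the only mismatch.

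**2. Time between enrolment and the rating.** Enrolment is at 2 to 12 weeks of infant age and the link is sent at 16 weeks. 16 − 12 = 4 weeks and 16 − 2 = 14 weeks, which reproduces the range given under Procedures.

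**3. Number of parents with a support rating.** Inputs from Sample size and condition allocation: a difference of half a standard deviation, 80% power, p < .05 (two-sided assumed), 20% dropout, recruitment target 152.

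- Plan's own figure: n per arm = 2 × (1.960 + 0.842)² / 0.5² = 62.8, so 63 per arm and 126 in total. Reproduced.
- Recruitment target: 126 × 1.20 = 151.2, so 152. Reproduced in that form. (Dividing by the retained fraction, 126 / 0.80 = 157.5, would give 158. That is a separate matter and does not bear on this point.)
- Respondents at 20% dropout: 152 × 0.80 = 121.6, about 122. Without a rating: 152 × 0.20 = 30.4, about 30.
- The Background cites retention of roughly 15% to 97% for online programs. If survey return fell anywhere in that range, respondents would number between 152 × 0.15 = 22.8 and 152 × 0.97 = 147.4.

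**4. Illustration of selection by return (all inputs assumed).** Let p be the share of enrolees with poor support, and rL and rH the return rates of poorly and better supported parents. The share seen among respondents is p·rL / [p·rL + (1 − p)·rH]. Take p = 20% and overall return 80%.

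- rL = 60%, rH = 85%: 0.12 / (0.12 + 0.68) = 15%.
- rL = 70%, rH = 82.5%: 0.14 / (0.14 + 0.66) = 17.5%.
- rL = 90%, rH = 77.5%: 0.18 / (0.18 + 0.62) = 22.5%.

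The first two understate poor support among enrolees by 5 and 2.5 points; the third overstates it by 2.5. Neither p, the return rates nor their ordering stands in the documents, so these lines show how the error arises, not how large it is. For scale, the standard error of a 20% share in 122 respondents is √(0.20 × 0.80 / 122) = 3.6 points, a 95% interval of about ±7 points.

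**The case against.** **The article may simply be abbreviated.** Its headings do not map strictly to time of measurement: system-logged program usage also stands under the follow-up questionnaire, and the statistical section names a within-subjects factor, which suggests more repeated measurement than the baseline section lists. The flow diagram is not available. This lowers confidence somewhat. But the baseline section is itemised and agrees with the objective on everything except support, and the support items are survey questions explicitly described elsewhere.

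**The consequence is easily overstated.** A reader might infer that the trial will report poorly supported parents as not reached. The documents do not support this. No population reference for support is named, and the Census comparison is promised only where possible. The Background's representation argument rests mainly on income, education, socioeconomic status and location, with social isolation mentioned in passing. Income, education and area-level disadvantage are taken at baseline. This objection stands.

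**Program effects on support are speculative.** Two of the three items concern the partner and relatives or friends outside the household. The program offers self-care content and links to support services, and nothing says it changes help from those people. The third item, on help from anyone, could more plausibly respond. The timing problem does not need a program effect, however: a rating at 16 weeks is not a rating at enrolment.

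**Missing data are handled.** Full Information Maximum Likelihood may reduce bias from non-return if data are missing at random. It cannot move the rating back to enrolment.

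**Baseline ratings have their own timing problem.** They would be taken at different infant ages in the two recruitment groups, while the protocol deliberately fixes follow-up by infant age. That is a real trade-off, but it applies to any enrolment measure, and the planned control for child age addresses it.

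**Conclusion.** The point holds for one variable. Read as written, the support part of the third objective describes follow-up respondents, about 122 of 152 at the planned dropout, and not the parents who enrolled. It may misstate both the enrolees' support and the difference between recruitment modes. The size and direction cannot be derived from the documents, and the illustrative shifts are smaller than the sampling error of the share itself.

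The conclusion rests on reading the baseline list as complete and the Caregiver support subsection as belonging to the follow-up survey only. If the full protocol also asks these items at enrolment, the point falls away. It would be wrong to conclude that the reach question as a whole is compromised, because the other listed characteristics are measured at entry. The objective concerned is descriptive, and the randomised comparison, the primary outcome and the sample size are untouched.

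**What to change.** - Add the three caregiver-support items to the baseline questionnaire and keep them at follow-up.
- Use the baseline answers for the third objective, adjusted for infant age at enrolment in line with the statistical section's control for child age.
- Recruitment has begun: the sample size rests on the first 20 participants randomised to the control condition. For parents already enrolled without a baseline rating, leave support out of the enrolment profile and report it only as a characteristic of follow-up respondents, by arm and recruitment mode.

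The cost is about one extra minute per parent and a minor amendment. The price in interpretation is that baseline ratings will be taken at infant ages from 2 to 12 weeks that differ by recruitment mode. The age adjustment will be weak where the two groups' ages overlap little, and the report should say so.
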